## Abstract

**Background:**

There are a variety of treatment options for Bell's palsy. Evidence from randomized controlled trials indicates corticosteroids can be used as a proven therapy for Bell's palsy. Acupuncture is one of the most commonly used methods to treat Bell's palsy in China. Recent studies suggest that staging treatment is more suitable for Bell's palsy, according to different path-stages of this disease. The aim of this study is to compare the effects of prednisolone and staging acupuncture in the recovery of the affected facial nerve, and to verify whether prednisolone in combination with staging acupuncture is more effective than prednisolone alone for Bell's palsy in a large number of patients.

**Methods/Design:**

In this article, we report the design and protocol of a large sample multi-center randomized controlled trial to treat Bell's palsy with prednisolone and/or acupuncture. In total, 1200 patients aged 18 to 75 years within 72 h of onset of acute, unilateral, peripheral facial palsy will be assessed. There are six treatment groups, with four treated according to different path-stages and two not. These patients are randomly assigned to be in one of the following six treatment groups, i.e. 1) placebo prednisolone group, 2) prednisolone group, 3) placebo prednisolone plus acute stage acupuncture group, 4) prednisolone plus acute stage acupuncture group, 5) placebo prednisolone plus resting stage acupuncture group, 6) prednisolone plus resting stage acupuncture group. The primary outcome is the time to complete recovery of facial function, assessed by Sunnybrook system and House-Brackmann scale. The secondary outcomes include the incidence of ipsilateral pain in the early stage of palsy (and the duration of this pain), the proportion of patients with severe pain, the occurrence of synkinesis, facial spasm or contracture, and the severity of residual facial symptoms during the study period.

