### Patients and enrolment

A power analysis is undertaken to calculate before conducting this trial: α = 0.05 and power = 80%. According to the previous literature, 70% of patients recover completely without treatment (placebo) compared with 80% of patients treated with prednisolone, acupuncture, or both. This difference of 10% is regarded as a clinically significant improvement. Therefore, the sample size in this trial can be estimated initially according to PASS software. Each group needs at least 172 patients (assuming a 15% dropout rate), 1200 patients in six groups will be enrolled in the study.

Baseline assessments before the start of treatment include neurological examination, grading of facial function, measurement of ipsilateral pain, documentation of concurrent medication. Patients with acute, unilateral, peripheral facial palsy, who are referred from neurology, internal medicine or emergency departments, or who seek care directly, are screened by physicians in 16 public county hospitals and Xijing hospital in Shaanxi province. There is at least one experienced neurology physician, who is responsible for implementing the study, with a special interest in facial palsy in each hospital. A written consent form will be obtained from each patient and retained by the investigators.

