#### Secondary Outcome

Pain around the ear, in the face, or in the neck will be registered on a visual analogue scale that ranges from 0 to 10 points, where 0 is no pain and 10 very severe pain. Occurrence of facial spasm or contracture and synkinesia in the different treatment arms at any time will be observed and recorded.

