### Statistics

The study will be performed using intention to treat. In this analysis, all randomized patients will receive at least one therapy, but patients who did not start treatment will be excluded (modified intention-to-treat analysis). The last-observation-carried-forward method will be used for the modified intention-to-treat analysis. The missing data points will be imputed in the post-baseline follow-up visits from the last observation available for each patient. An interaction test was done to show the synergistic effect of the combination of prednisolone and acupuncture. Categorical variables will be compared by using Fisher's exact test. Cox proportional hazards models will be used to estimate the hazard ratio (HR) of recovery, including 95% CI. These will be compared between groups by using t-test, and Mann-Whitney, or Chi-squared tests as appropriate. All statistical assessments are two-sided, and a P value < 0.05 is considered statistically significant.

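### Pain is registered on a 0–10 scale, but the only pain-intensity outcome the article names is a cut of that scale (the proportion with severe pain)

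*Protocol article*

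**What the plan says.** - **How pain is recorded** (Protocol article, Secondary Outcome): pain around the ear, in the face or in the neck is "registered on a visual analogue scale that ranges from 0 to 10 points, where 0 is no pain and 10 very severe pain".
- **Baseline** (Patients and enrolment): "Baseline assessments before the start of treatment include neurological examination, grading of facial function, measurement of ipsilateral pain".
- **Pain outcomes named** (Abstract, Methods/Design): "The secondary outcomes include the incidence of ipsilateral pain in the early stage of palsy (and the duration of this pain"), followed by "the proportion of patients with severe pain".
- **Tests** (Statistics): "Categorical variables will be compared by using Fisher's exact test". The same section adds "These will be compared between groups by using t-test, and Mann-Whitney, or Chi-squared tests as appropriate". No test is tied to pain.

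The article gives no expected pain level, no standard deviation and no expected share with severe pain.

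**The concern.** Of the three pain outcomes named, incidence asks whether there is pain and duration asks how long it lasts. Only the third concerns how bad it is, and it reduces an 11-point score to yes or no. As a categorical variable it falls to Fisher's exact test, which cannot use the pain score taken before treatment. Any change that stays on one side of the cut then counts as no difference.

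At stake is the power to detect an effect of prednisolone or acupuncture on pain intensity. If severe pain is uncommon, each arm has few events, and a moderate reduction in pain could be reported as no difference.

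**Working it through.** The article states no figure for pain, so there is nothing to reproduce. Its sample size rests on complete recovery and does not bear on this point. From the article come the 0–10 scale, two-sided α = 0.05, and 1200 / 6 = 200 patients per group if allocation is equal. The share with severe pain (p), the share pain-free and the effect sizes below are all assumptions.

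**1. Information kept by the cut, normal-score model.** Fraction kept = φ(z_p)² / [p(1 − p)].

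| p severe | φ(z_p) | calculation | kept | lost |
|---|---|---|---|---|
| 5% | 0.1031 | 0.01064 / 0.0475 | 22% | 78% |
| 10% | 0.1755 | 0.03080 / 0.09 | 34% | 66% |
| 20% | 0.2800 | 0.07838 / 0.16 | 49% | 51% |
| 30% | 0.3477 | 0.1209 / 0.21 | 58% | 42% |
| 50% | 0.3989 | 0.1592 / 0.25 | 64% | 36% |

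More than half is lost only if fewer than about 21% of patients are severe.

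**2. The same question with many zeros, proportional-odds model.** Fraction kept = 3p(1 − p) / (1 − Σp_i³), summed over the eleven score values. I spread the mild share evenly over 1–6 and the severe share evenly over 7–10; other even splits change little. The last column is the power of the cut when a full-scale analysis has 80%, from Φ(2.80 × √fraction − 1.96).

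| severe / pain-free | calculation | kept | power of the cut |
|---|---|---|---|
| 20% / 30% | 0.48 / 0.969 | 50% | about 50% |
| 10% / 50% | 0.27 / 0.873 | 31% | about 34% |
| 5% / 70% | 0.1425 / 0.657 | 22% | about 26% |

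The two models nearly agree. At 10% severe the loss is 66% under the first and 69% under the second.

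**3. Power example.** With 200 per group and an assumed shift of 0.3 SD in a normal score, comparing the score has 85% power. A two-proportion comparison of the cut has 24% (5% severe), 36% (10%), 51% (20%), 59% (30%) and 66% (50%).

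**4. Simulation with a spike at zero.** There are 200 patients per arm. Pain among those affected is a rounded normal (mean 4.5, SD 2.2) on 1–10, and treatment lowers it by 0.7. The pain-free share is 30–70%, and severe means 6 or more, or 7 or more. The baseline-adjusted comparison assumes a baseline correlation of 0.5.

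| Effect | Fisher on the cut | Mann-Whitney, unadjusted | Score, baseline-adjusted |
|---|---|---|---|
| Intensity, and odds of no pain × 1.5 | 25–64% | 51–84% | 65–92% |
| Intensity only | 11–42% | 5–32% | 14–46% |

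The adjusted column comes from a separate run, in which Fisher on the cut had 25–63% and 12–40%. When the pain-free share also changes, the full score is clearly better. Under a pure intensity effect, the unadjusted score ties with or loses to the cut, and the adjusted score is slightly ahead or about equal.

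**The case against.** The strongest reply is that the article never says the score will go unanalysed. The outcome list is in the abstract and opens with a word that leaves it open. The Secondary Outcome section speaks only of the 0–10 scale and mentions no cut. The Statistics section offers a t-test and Mann-Whitney. This stands: a reader might infer that pain will be judged solely by the severe-pain proportion, and the document does not support that. It supports only the statement that no other intensity outcome is named. Matching tests to secondary outcomes, adjusting for baseline and defining severe may all be in a fuller document, so their absence is not counted here. Naming the intensity outcome as a proportion is a choice the article itself makes.

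A second reply is that the other pain outcomes carry much of the scale. By the formula in step 2, a none/any cut keeps 0.63 / 0.969 = 65%, 0.75 / 0.873 = 86% and 0.63 / 0.657 = 96% in the three scenarios. None/some/severe taken together keeps about 87%, 93% and 98%. So a reader who concludes that most of the scale is thrown away goes too far. Two limits remain: separate tests do not pool this information, and incidence is restricted to the early stage of palsy.

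A third reply is that the full score does not always win. That is correct, as the last row of the simulation shows.

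**Conclusion.** The point holds as a minor one on a secondary outcome. The article collects a graded score, with a baseline value, and names only a cut of it for intensity. If intensity is judged by that cut with Fisher's exact test, the loss is about 36% at a median split, about half at 20% severe, and 66–78% at 5–10% severe. These figures rest on assumed shares and on a normal-score or proportional-odds model. Incidence and duration recover part of the loss.

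The benefit of the full score is substantial if treatment also changes the share who are pain-free, and small or nil if it changes intensity only among those with pain. The gain from adjustment depends on the assumed baseline correlation of 0.5. No stated figure is contradicted and the primary conclusion is not affected.

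**What to change.** Name the 0–10 pain score as the pain-intensity outcome, at whatever follow-up visits pain is recorded. The article's visit schedule is stated for facial function, so the pain visits should be confirmed. Compare arms with a model adjusted for the baseline pain score: proportional-odds, or a repeated-measures model if several visits are used. Keep the severe-pain proportion as a supporting summary beside incidence and duration.

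The cost is a change of wording. Pain is already scored on this scale and measured at baseline. The downside is that the effect becomes a mean difference or a common odds ratio, which is less immediate to a clinical reader than a difference in proportions.

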**Discussion:**

The result of this trial will assess the efficacy of using prednisolone and staging acupuncture to treat Bell's palsy, and to determine a best combination therapy with prednisolone and acupuncture for treating Bell's palsy.

**Trial Registration:**

ClinicalTrials.gov: NCT01201642

## Background

Bell's palsy is an acute peripheral unilateral facial weakness or paralysis with an as yet unknown cause. Bell's palsy accounts for almost three quarters of peripheral facial palsies and the annual incidence is about 30 patients per 100 000. 71% of untreated patients with Bell's palsy will completely recover and 84% will have complete or near normal recovery. The remainder will have persistent moderate to severe weakness, facial contracture, or synkinesis [1-3]. Because of its unclear etiology, there has been longstanding controversy about what treatment should be given, with potential alternatives including corticosteroids, antiviral drugs, acupuncture and physiotherapy. Inflammation of the facial nerve is the most probable cause of Bell's palsy. Therefore corticosteroids are commonly used as treatment of Bell's palsy. A recent study shows significant short-term and long-term positive treatment effects of prednisolone in patients with Bell's palsy [4].

Acupuncture is a safe therapy with a low risk of adverse events in clinical practice [5]. It is one of the most commonly used treatments for Bell's palsy in China. Chinese traditional acupuncture is low cost and very convenient to local people. Though only limited experience has been reported with acupuncture for Bell's palsy [6], several studies provide increasing evidence for a beneficial effect of acupuncture as an adjunctive treatment of Bell's palsy [7-10]. Bell's palsy has different path-stages; it includes acute stage (1-7 days onset of disease), resting stage (8-20 days onset of disease) and restoration stage (21-90 days onset of disease) [11-14]. However, convincing evidence for the efficacy of staging acupuncture to treat Bell's palsy is lacking because of previous poor study designs, small sample sizes or unclear reporting treatment. It's not clear whether acupuncture is effective in different path-stages.

Thus, in view of these data, we designed this randomized controlled multicentre study of Bell's palsy patients, with the aim of comparing the effects of prednisolone and staging acupuncture in the recovery of the affected facial nerve. We also hoped to verify whether staging acupuncture along with prednisolone is more effective than prednisolone alone in larger number of patients, especially in terms of reducing their level of incapacity and improving their quality of life.

## Methods/Design

### Overview

This is a multicentre, randomized, placebo-controlled study (Figure 1). This study has been approved by the ethical committees of Xijing hospital and is registered with ClinicalTrials.gov database (reference no. NCT01201642). The study will be conducted according to the Declaration of Helsinki.

**Figure 1 F1:**
[figure not shown]
**Flow chart of the trial, describing the selection, randomization and follow-up process**.

### Patients and enrolment

A power analysis is undertaken to calculate before conducting this trial: α = 0.05 and power = 80%. According to the previous literature, 70% of patients recover completely without treatment (placebo) compared with 80% of patients treated with prednisolone, acupuncture, or both. This difference of 10% is regarded as a clinically significant improvement. Therefore, the sample size in this trial can be estimated initially according to PASS software. Each group needs at least 172 patients (assuming a 15% dropout rate), 1200 patients in six groups will be enrolled in the study.

Baseline assessments before the start of treatment include neurological examination, grading of facial function, measurement of ipsilateral pain, documentation of concurrent medication. Patients with acute, unilateral, peripheral facial palsy, who are referred from neurology, internal medicine or emergency departments, or who seek care directly, are screened by physicians in 16 public county hospitals and Xijing hospital in Shaanxi province. There is at least one experienced neurology physician, who is responsible for implementing the study, with a special interest in facial palsy in each hospital. A written consent form will be obtained from each patient and retained by the investigators.

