### Randomization

Patients are to be randomly assigned to one of six treatment groups. A computer-generated allocation sequence (in permuted blocks with a block size of 12) will be created by an operator who is not directly involved with the study. Once created, the allocation sequence will be kept in a secure locked drawer making it inaccessible to all study personnel. Allocation concealment will be achieved using sequentially numbered sealed envelopes which are opaque when held to the light. When a patient is enrolled in the study, an independent researcher will be contacted and asked to give the next numbered envelope to the physician who will make up the medications to be used in the study. The independent researcher will record the patient's details and the number of the envelope assigned to that patient. This procedure ensures that the randomization is not influenced by the researchers taking part in this study.

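### At least 172 patients per group does not give 80% power to compare one active group with placebo at 70% vs 80% recovery; power is about 51% to 71%, depending on test and number analysed

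*Protocol article*

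**What the plan says.** Patients and enrolment in the protocol article sets "α = 0.05 and power = 80"%. The rates are "70% of patients recover completely without treatment (placebo) compared with 80% of patients treated with prednisolone, acupuncture, or both", and the gap is justified clinically: "This difference of 10% is regarded as a clinically significant improvement". The result, attributed to PASS software, is "Each group needs at least 172 patients (assuming a 15% dropout rate), 1200 patients in six groups will be enrolled in the study".

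Three other places bear on the calculation:

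- Statistics fixes the sidedness: "All statistical assessments are two-sided, and a P value < 0.05 is considered statistically significant".
- Randomization allocates "in permuted blocks with a block size of 12", which over six groups fits two per group per block. The ratio itself is not stated.
- The Background paragraph of the abstract gives as one aim "to verify whether prednisolone in combination with staging acupuncture is more effective than prednisolone alone".

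The article does not say which contrast or test was entered in PASS, or whether 172 is before or after dropout.

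**The concern.** The article prints both the inputs and the answer, so the answer can be checked. A requirement stated for each group, with one rate for placebo and one for treatment, reads most naturally as one group against another. On that reading 172 is far too small for 80% power.

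A reader who trusts the 80% figure would take a non-significant result as fair evidence against a 10-point gain. With true power between a half and about 70%, it would be much weaker evidence. This matters here because the Discussion expects the trial to settle whether prednisolone alone does as well as prednisolone with acupuncture, a question on which a null result is easily over-read.

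**Working it through.** **Inputs.** Placebo 0.70, active 0.80, alpha 0.05, power 80%, 172 per group, 15% dropout and 1200 enrolled, all from Patients and enrolment; two-sided tests, from Statistics. Equal allocation (200 per group) is an assumption, consistent with blocks of 12. No adjustment for multiple comparisons is made below.

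**1. Trying to reproduce 172 for two equal groups.** Pooled two-proportion formula, mean rate 0.75:

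n = [1.96·√(2·0.75·0.25) + 0.8416·√(0.21 + 0.16)]² / 0.10² = (1.2002 + 0.5119)² / 0.01 = 293.2, so 294 evaluable per group.

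Variants of the same comparison:

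| Method | n per group |
|---|---|
| Unpooled variance | 291 |
| Arcsine | 292 |
| Continuity-corrected | 313 |
| One-sided | 231 |
| Six-group chi-square, 5 df | 261 |

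None gives 172, before or after division by 0.85. With 15% dropout, 294/0.85 = 346 per group, or 2076 in six groups.

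**2. Power of a test of proportions.** Power = Φ{[0.10·√n − 1.2002] / √0.37}, with √0.37 = 0.6083.

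| Analysed per group | Meaning | z | Power |
|---|---|---|---|
| 146 | 172 already includes dropout (172 × 0.85) | 0.013 | 50.5% |
| 170 | 200 less 15% | 0.170 | 56.8% |
| 172 | stated minimum, all evaluable | 0.183 | 57.3% |
| 200 | everyone enrolled is analysed | 0.352 | 63.8% |

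**3. Power of a log-rank test.** The abstract defines the primary outcome as time to complete recovery, and Statistics plans Cox models. Assume proportional hazards, with 70% and 80% recovered by the end of follow-up.

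- HR = ln 0.2 / ln 0.3 = 1.337, and ln HR = 0.290.
- Events needed = 4·(1.96 + 0.8416)² / 0.290² ≈ 373.
- With 75% recovering on average, 373 / (2 × 0.75) ≈ 249 per group.
- Power = Φ(½·√(1.5n)·0.290 − 1.96): about 57% at 146, 64% at 170 to 172, and 71% at 200.

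**4. Placebo against all five active groups pooled (1:5).** The mean rate is (0.7 + 5 × 0.8)/6 = 0.7833.

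n(placebo) = [1.96·√(0.7833·0.2167·1.2) + 0.8416·√(0.21 + 0.16/5)]² / 0.01 = (0.8845 + 0.4140)² / 0.01 ≈ 168.6, so 169.

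With 172 against 860, power is 80.7%. With 146 placebo patients it is 74%.

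**5. What the trial can detect.** Solving the formula in step 2 for 80% power against 70% on placebo gives an active rate of about 82.9% with 170 analysed per group, and about 81.9% with 200.

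**6. Combination against prednisolone alone.** The paragraph assigns 80% to both. The assumed difference is zero, so there is no effect for the calculation to power.

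**7. Dropout.** If 172 is the evaluable number, 172/0.85 = 202.4, so 203 per group are needed (1218 in total). If 172 already includes dropout, 200 exceeds it.

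**The case against.** The strongest defence is the pooled reading. The paragraph gives a single rate for patients on prednisolone, acupuncture or both, which can be taken literally as all treated patients against placebo. That contrast needs 169 placebo patients, and 172 gives 80.7%. A reader might therefore go too far in saying that 172 cannot follow from the stated inputs; the article does not name its contrast, so that is not shown. The defence still does not rescue the claim. No pooled contrast is described anywhere, the stated aims compare individual groups, and the reading falls to 74% if 172 already includes dropout. A one-sided 1:2 comparison needs 171, and a one-sided log-rank test about 196 to 199, close to the 200 enrolled. Both conflict with the two-sided rule in Statistics.

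The second defence concerns the number analysed. A reader might infer that the trial would miss a true 10-point gain more than four times in ten. That follows for a test of proportions with about 170 analysed, but the documents do not fix 170. The modified intention-to-treat analysis removes only patients who never start treatment, and last observation carried forward keeps those lost later. Close to 200 per group could be analysed, and the miss rate would then be about 36% for proportions or 29% for a log-rank test. This objection stands, so the power must be given as a range.

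Third, the dropout arithmetic might be read as a separate error. It is one only if 172 is the evaluable number, and going from 172 to 170 moves power by half a point.

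**Conclusion.** The point holds for group-against-group comparisons. At a two-sided 5% level, 80% power for 70% vs 80% needs about 294 evaluable per group (about 249 for a log-rank test under proportional hazards). The planned numbers give about 51% to 64% for a test of proportions and about 57% to 71% for a log-rank test, depending on whether 146, 170 to 172 or 200 are analysed. No two-sided comparison of two equal groups reaches 80%. The results assume equal allocation and no multiplicity adjustment.

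How 172 arose cannot be told from the article. What can be said is that the one two-sided reading found near it is undescribed and does not serve the aims. The comparison of combination with prednisolone has no power basis under the assumed rates. The dropout discrepancy (203 against 200 per group) is minor and conditional.

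**What to change.** Keep 1200 patients and rewrite the sample size paragraph:

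- Name the contrast and the test entered in PASS, and say whether 172 is before or after dropout.
- Replace the 80% claim with the actual power. Suggested text: *With 200 patients randomised per group, a two-sided 5% comparison of one active group with placebo has about 57% power (170 analysed per group) to 64% power (200 analysed) for 70% vs 80% complete recovery, and 80% power for 70% vs about 82% to 83%.* If the main analysis is time to recovery, give the log-rank figures (about 64% and 71%) with the proportional hazards assumption.
- State that the assumed rates, 80% for both prednisolone and the combination, provide no power basis for comparing these two.
- If 172 proves to be the evaluable number, inflate by dividing by 0.85 and note that 200 per group falls slightly short of 203.

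The cost is one paragraph and a less favourable power figure. No extra patients are needed and the design does not change.
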